## Abstract

**Objective::**

The study aims to investigate the efficacy of TEAS for hypertension, and to screen the optimal electrical stimulation frequency.

**Methods::**

This is an 8-week, randomized, controlled pilot trial with 3 parallel groups. In a ratio of 1:1:1, 120 patients with stage 1 hypertension will be divided into the TEAS-2Hz group, TEAS-10Hz group, or usual care group. All patients will receive the usual care for hypertension including lifestyle education, etc. Additionally, the 2 TEAS groups will receive 12 sessions of TEAS interventions at 2 Hz or 10 Hz, 3 times weekly for 30 minutes each, with 4 weeks of follow-up. The main outcome will be the change from baseline to week 4 in systolic BP among the groups. Secondary outcomes consist of changes in diastolic BP, mean arterial pressure, heart rate, heart rate variability, medication adherence, and quality of life. The safety outcomes will be any adverse event during the treatment.

**Discussion::**

As a pre-study for the next large clinical trial of TEAS for hypertension, this study will offer references for optimized frequency of biofeedback electrical devices and promote more consciousness of the benefits of body-mind holistic regulation of BP, thereby achieving proactive and overall process management of BP.

## 1. Introduction

Hypertension, the most prevalent chronic condition, is regarded as the leading risk factor for cardiovascular disease and renal diseases.^[1–3]^ In 2019, high systolic blood pressure (BP) was the dominant hazard factor for attributable mortality globally, accounting for 19.2% of total deaths.^[4]^ Hypertension with increasing prevalence imposes a heavy burden of diseases worldwide.^[5,6]^ Although long-term adherence to lifestyle interventions and antihypertensive medication are recommended by various guidelines for hypertension, fewer than 50% of those on treatment had achieved BP control.^[7–10]^ Difficulty in lifestyle changes and limitations in pharmacotherapy owing to adverse effects, expense, and compliance of patients are primarily responsible for uncontrolled BP.^[11,12]^ As a consequence, a wider range of antihypertensive interventions are increasingly required for the needs of distinct hypertensive groups.

Acupuncture, a vital component of traditional Chinese medicine, has been utilized as a nondrug therapy for treating patients with cardiovascular disease.^[13–15]^ Although the conclusions are varied, most studies suggest that acupuncture is effective in lowering BP as an adjunctive therapy.^[3,16–18]^ Transcutaneous electrical acupoint stimulation (TEAS), as the electrical stimulation portion of biofeedback physical regulation based on acupoints, is a novel acupuncture technique that is noninvasive, integrating the functions of modern transcutaneous electrical nerve stimulation (TENS) and conventional acupoint stimulations.^[19]^ By applying electro-stimulation pulses on aimed acupoints, TEAS delivers similar effects to electroacupuncture, but without the risks of invasive infection, patients psychological fears, or manipulator bias.^[20]^ Meanwhile, Along with the stimulation sites, the stimulation parameters are another crucial factor in the efficacy of TEAS. Evidence for a potential hypotensive effect of TEAS has been provided by some studies, but the optimal stimulation parameters remain unclear.^[21–23]^ The stimulation parameters of TEAS mainly consist of intensity, waveform, and frequency, among which the frequencies used vary widely in different studies, ranging from low frequency to high frequency.^[24,25]^ Studies find that both high frequency and low frequency electrical stimulation have shown some vasodilatory effects.^[26,27]^ but for decreasing BP, low frequency seems to perform better, which may also correlate with its modulation of autonomic nerves.^[21,28,29]^ Also, the low frequency of electrical stimulation is a wide range that requires to be selected optimally.

Based on the above, the pilot trial is expected to investigate the effectiveness and safety of TEAS for hypertension by comparing it with usual care; to explore the optimal transcutaneous electrical stimulation frequency by comparing different stimulation frequencies at 2 Hz and 10 Hz. Further, it will lay a foundation for future large clinical trials and provide a reference for the parameter setting of biofeedback electric stimulation devices.

## 2. Methods

### 2.1. Study design

This study is a randomized, controlled pilot trial with 3 parallel groups. A total of 120 hypertensive patients meeting the inclusion criteria will be recruited and then randomly allocated to 3 groups of 40 patients each. All 3 groups will receive 4 weeks of usual care, and TEAS intervention groups will be additionally treated with TEAS treatment (2 Hz or 10 Hz). We will keep the stimulation location, duration, waveform, and other parameters the same for comparing the effects of different frequencies of TEAS in hypertension. The study protocol has obtained approval from the ethics committee of Beijing University of Chinese Medicine (No. 2022BZYLL1207), as well as registration at the Chinese clinical trial registry (ChiCTR2200067147). The protocol will be reported in compliance with the Standard Protocol Items (SPIRIT). The outline of the study protocol is displayed in a flow chart (Fig. 1), while the schedule of the trial process is illustrated in Table 1.

**Figure 1. F1:**
[figure not shown]
Flow chart of the trial. TEAS = transcutaneous electrical acupoint stimulation.

**Table 1 F3:**
[figure not shown]
Schedule of the trial process.

### 2.2. Recruitment

The 120 participants will be screened and recruited from hospitals in Beijing. Recruitment information will be acquired by patients mainly through posters, flyers, and social media. The trained researchers will screen patients following inclusion and exclusion criteria. Patients who meet the requirement will sign informed consent before enrollment.

### 2.3. Participants

#### 2.3.1. Inclusion criteria.

Systolic blood pressure (SBP) of 140 to 159 mm Hg and/or diastolic blood pressure (DBP) of 90 to 99 mm Hg for individuals not taking antihypertensive drugs; SBP of 120 to 159 mm Hg and/or DBP of 80 to 99 mm Hg for individuals taking antihypertensive drugs with no change in the last month.Aged 18 to 65 years old, regardless of gender.No hearing and comprehension disabilities to complete the questionnaire.Willing to participate in clinical observation and sign an informed consent form.

#### 2.3.2. Exclusion criteria.

Patients with secondary hypertension: such as acute and chronic glomerulonephritis, renal artery stenosis, gestational hypertensive syndrome, pheochromocytoma, primary aldosteronism, etc.Contraindications to the use of electrical stimulation devices: with pacemakers or other implantable devices; suffering from acute illnesses, contagious diseases, and other malignant diseases; in pregnancy or lactation; breakage, inflammation, scarring, etc, at the skin of the acupuncture point; sensory impairment or allergy to electrical stimulation, etc.Have taken medications other than antihypertensive drugs that may affect BP, such as glucocorticoids, in the past month.Have received acupuncture or transcutaneous electrical stimulation treatment in the past year.

### 2.4. Randomization and masking

Participants enrolled in this trial will be equally allocated to the TEAS-2Hz group, TEAS-10Hz group, or usual care group by block randomization. The computer-generated random sequence will be created by an independent statistician and preserved by an investigator not involved in this trial. Every patient’s random number is to be accessed by telephone from the noninvolved investigator. Due to the trial design, participants of the usual care group will inevitably know about their grouping.

To ensure that the participants receiving TEAS and the TEAS operators will remain blinded to the allocation (2Hz or 10Hz) during the entire study, an independent investigator will set up the frequency of the stimulation device in advance and then cover the frequency display site. The distribution of the 3 groups will be hidden from the outcome evaluators and data analysts.

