### 2.5. Intervention

If the participants are taking regular antihypertensive drugs, they can keep taking their medication. Every patient’s medication usage will be recorded throughout the trial by the researchers, who will also provide lifestyle education to all participants during the treatment period, such as sending information about the impact of lifestyle on BP and other related scientific knowledge.

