### 2.6. Primary outcome

The primary outcome will be the change in office SBP among the 3 groups from baseline to the end of the intervention (week 4). The measurement of BP will be performed with an electronic sphygmomanometer (KC2110, Shaanxi Kangshengshi Electronic Technology Co., Ltd., Shaanxi, China). Patients will be required to sit in silence for at least 5 minutes before taking their BP. Keeping the upper arm at the level of the heart, both arms will be measured at baseline and the side with the higher BP will be chosen for subsequent testing. To ensure the accuracy of the recording, the independent outcome assessor will repeat the BP measurement 3 times every 5 minutes and take the mean of the last 2 readings.

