### 2.9. Sample size calculation

This pilot trial focuses on the effects of TEAS for hypertension and the optimal stimulation frequency, so as to be a preliminary for the further clinical trial. In accordance with Provisions for Drug Registration in China, the minimum number of cases (experimental group) for exploratory clinical trials is required to be 20 to 30. Browne^[34]^ considers that a sample of 30 cases is not sufficient to ensure confidentiality unless the effect size is very large. Kieser et al^[35]^ and Hertzog^[36]^ recommended 20 to 40 cases as an empirical estimate of the sample size for pretesting. Accordingly, taking full consideration of the above recommendations and the shedding rate, 40 participants per group and a total of 120 participants in 3 groups were determined.

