### 2.10. Statistical analysis

The statistical software IBM SPSS Statistics (25.0, NY) will be selected for data analysis. Statistical analysis will be conducted following the principle of intention-to-treat (ITT), which involves all patients randomly assigned in the trial for ensuring the randomization principle. Missing data will be processed by the method of multiple imputation. Continuous data will be indicated as mean ± standard deviation or median and interquartile range, based on whether the normality is satisfied. As for measurements at different time points, repeated measures ANOVA and Bonferroni post hoc tests will be used for evaluation. Categorical data will be described as frequencies and percentages, and the difference among groups will be analyzed by the chi-square test or Fisher exact test. In a 2-sided test at *P* < .05, the difference will be deemed statistically significant.

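### Antihypertensive drug use sets the entry limits but appears in neither the described allocation nor the stated analysis: a modest, near-free gain in precision is left unused

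*Protocol article*

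**What the plan says.** **Allocation.** Section 2.4 of the protocol article states that participants "will be equally allocated to the TEAS-2Hz group, TEAS-10Hz group, or usual care group by block randomization". It describes who creates and holds the sequence and how it is accessed by telephone. It names no stratification factor.

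**Entry.** Section 2.3.1 sets limits by drug status. The first limit is "Systolic blood pressure (SBP) of 140 to 159 mm Hg and/or diastolic blood pressure (DBP) of 90 to 99 mm Hg for individuals not taking" such drugs; the second is "SBP of 120 to 159 mm Hg and/or DBP of 80 to 99 mm Hg for individuals taking antihypertensive drugs", with treatment unchanged in the last month.

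**Treatment during the trial.** Section 2.5 says: "If the participants are taking regular antihypertensive drugs, they can keep taking their medication". Each patient's drug use is recorded throughout.

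**Size, endpoint and analysis.** Section 2.9 says that "40 participants per group and a total of 120 participants in 3 groups were determined", by rule of thumb; it gives no effect size, SD, power or dropout rate. The primary outcome (section 2.6) is the change in office SBP from baseline to week 4. For measurements over time, section 2.10 says that "repeated measures ANOVA and Bonferroni post hoc tests will be used for evaluation". It names no covariate.

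**The concern.** By setting separate limits, the protocol itself treats drug status as relevant to blood pressure. The status is known before randomisation. Users and non-users may differ in starting SBP and in how far SBP moves over four weeks, whatever the arm. As described, neither the allocation balances this factor nor the analysis adjusts for it.

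At stake is precision, and how the single result can be read. The trial is meant to help choose between 2 Hz and 10 Hz and to inform a larger trial. If one arm happens to hold clearly more drug users, part of an observed difference in SBP change could reflect that mix, and the stated analysis has no term to separate the two.

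**Working it through.** **Inputs from the article:** three arms of 40 (3 × 40 = 120, which agrees with the stated total); endpoint is change in SBP to week 4; two-sided 5% test. The sample size comes from a rule of thumb, so there is no power calculation to reproduce.

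**Assumptions, because the article gives no figures:** share on drugs 30%, 50% or 70%; SD of SBP change 10 or 12 mm Hg; difference in mean change between users and non-users, g, of 2, 4 or 6 mm Hg.

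**Step 1: chance imbalance in drug use.** With K users among 120 and allocation that ignores drug use, the numbers of users per arm are hypergeometric. For a share p, the SD of the difference between two arms is √[p(1−p) × (2/40) × (120/119)]:
- p = 0.5: √(0.25 × 0.05 × 1.0084) = 0.112
- p = 0.3 or 0.7: √(0.21 × 0.05 × 1.0084) = 0.103

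A simulation of 200,000 draws gives:

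| Share on drugs | Given pair differs by ≥ 20 points | Some pair of the three does | 95th percentile, given pair |
|---|---|---|---|
| 30% | 0.068 | 0.166 | 20 points |
| 50% | 0.095 | 0.221 | 22.5 points |
| 70% | 0.067 | 0.164 | 20 points |

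**Step 2: effect on the primary endpoint.** Shift in the estimated difference in change = g × imbalance. At the 95th percentile (0.20 to 0.225):
- g = 2: 0.40 to 0.45 mm Hg
- g = 4: 0.80 to 0.90 mm Hg
- g = 6: 1.20 to 1.35 mm Hg

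The standard error of a pairwise difference is SD × √(2/40) = 2.24 mm Hg (SD 10) or 2.68 mm Hg (SD 12). The shift is therefore between 0.40/2.68 = 0.15 and 1.35/2.24 = 0.60 of a standard error.

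**Step 3: type I error over all allocations.** A simulated unadjusted one-way ANOVA on change (20,000 runs, half on drugs, within-stratum SD 10) rejects at 0.048, 0.050 and 0.049 for stratum differences of 0, 6 and 10 mm Hg. It stays at its nominal level.

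**Step 4: type I error given a bad draw.** For a 20-point imbalance, take the shift divided by the standard error, with the variance of the test statistic reduced by the stratum part. For g = 6 and SD 10 the standardised shift is 1.2/2.236 = 0.537, and the statistic's SD is √0.91 = 0.954. The tail probabilities are P(Z > 1.49) + P(Z < −2.62) ≈ 0.068 + 0.004 = 0.072. Over SD 10 to 12, the pairwise error before Bonferroni is 0.066 to 0.072 for g = 6, and 0.057 to 0.060 for g = 4.

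**Step 5: gain from stratifying and adjusting (half on drugs).** The variance of change falls from SD² to SD² − g²/4. Power is for an assumed 6 mm Hg effect, two-sided 5%, before Bonferroni.

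| SD | g | SE before | SE after | Power before | Power after |
|---|---|---|---|---|---|
| 10 | 2 | 2.24 | 2.22 | 0.765 | 0.769 |
| 10 | 4 | 2.24 | 2.19 | 0.765 | 0.782 |
| 10 | 6 | 2.24 | 2.13 | 0.765 | 0.803 |
| 12 | 2 | 2.68 | 2.67 | 0.609 | 0.612 |
| 12 | 4 | 2.68 | 2.65 | 0.609 | 0.621 |
| 12 | 6 | 2.68 | 2.60 | 0.609 | 0.637 |

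**The case against.** The strongest case is that this is silence in a condensed article rather than a fault. The full protocol may hold stratification factors and covariates, and simple blocking is a legitimate choice for a pilot sized by rule of thumb. Chance imbalance under valid randomisation is already part of the standard error, and drug use is recorded, so it can be described or adjusted for later.

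Much of this stands. The article does not say that stratification is absent; it only describes a scheme and an analysis without it. The unconditional error rate is intact (step 3). What does not fall away is that the trial is run once: given a bad draw, an unadjusted comparison is somewhat off its nominal level (step 4), and a factor already collected would correct for it.

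A reader might also infer more than the article supports:
- **Two separate SBP populations.** The ranges overlap from 140 to 159 mm Hg, and the and/or wording lets a patient enter on diastolic pressure alone, so SBP can lie below either floor.
- **A 2 mm Hg distortion.** Range midpoints of 149.5 and 139.5 differ by 10 mm Hg, and a 20-point imbalance gives 10 × 0.20 = 2 mm Hg. That is a shift in baseline SBP resting on assumed midpoints. The endpoint is change, to which a baseline shift does not carry over one for one.
- **Protection of heart rate and heart rate variability from drug class effects.** An on/off stratum does not balance drug class, so this is no argument for it.

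**Conclusion.** The point holds as a minor design improvement. It is neither an error nor a contradiction in the article. As described, a factor that the entry criteria themselves use is handled in neither allocation nor analysis. The reading that the randomisation is defective or the comparison biased is not supported.

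The consequence is a roughly 1 in 6 to 1 in 5 chance that some pair of arms differs by 20 points or more in drug use (7% to 9.5% for a given pair). In such a draw, the endpoint shifts by about 0.15 to 0.6 of a standard error. The probabilities rest on the assumed share of drug users. The shift and the power gain also rest on the assumed SD and on an assumed difference in mean change between users and non-users. If the two strata change alike, nothing is lost.

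**What to change.** 1. Include baseline antihypertensive drug use (yes/no) as a factor in the week-4 SBP model. If the repeated measures model is kept, enter it with its interaction with time, because a main effect alone adjusts levels and not change.
2. If recruitment has not started, generate the block sequence separately for patients on and not on antihypertensive drugs at baseline. If it has started, keep the sequence and make only the first change, which recovers most of the precision.
3. If the full protocol already does either, say so in sections 2.4 and 2.10.

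The cost is one extra model term, one extra list for the independent statistician and one extra item in the existing telephone call. No additional data are needed.

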### 2.5. Intervention

If the participants are taking regular antihypertensive drugs, they can keep taking their medication. Every patient’s medication usage will be recorded throughout the trial by the researchers, who will also provide lifestyle education to all participants during the treatment period, such as sending information about the impact of lifestyle on BP and other related scientific knowledge.

#### 2.5.1. Usual care group.

Participants assigned to the usual care group will not be treated with TEAS interventions.

#### 2.5.2. TEAS groups.

To exploratively observe the hypotensive effect of different stimulation frequencies, this trial will set up 2 TEAS groups, in which patients will respectively receive TEAS at 2 Hz or 10 Hz, with the addition of their routine care. The interventions will last for 12 sessions of 30 minutes each, 3 sessions per week for 4 weeks. The treatment will be conducted using the TENS mode of a low frequency pulse electroacupuncture instrument (XS-998B06, Nanjing Xiaosong Medical Instrument Research Institute, Nanjing, China).

Every instrument has 6 output channels, each connected to a pair of square electrodes (40 mm × 40 mm). The patient is expected to fully expose the acupoints of the limbs in a comfortable sitting position. After cleaning the skin, bilateral acupoints will be applied by electrodes. Each pair of electrodes is connected to 3 groups of acupoints on the same side of the limb, and the acupoints are Quchi (LI11) and Hegu (LI4), Neiguan (P6) and Ximen (PC4), Zusanli (ST36) and Taichong (LR3). Figure 2 shows the location of the acupoints and the connection method with the instrument. The instrument outputs a bidirectional symmetrical narrow square wave with a pulse width of 0.4 ms-0.6 ms. The output frequency will be set at 2 Hz or 10Hz depending on the grouping of patients. The stimulation intensity of each output is adjusted to the maximum intensity tolerated by the participant and causes no pain or discomfort, and the stimulation will last for 30 minutes.

**Figure 2. F2:**
[figure not shown]
Acupoint locations (right limb as an example) and instruments for interventions and evaluations. TEAS = transcutaneous electrical acupoint stimulation; LI11 = Quchi; LI4 = Hegu; PC6 = Neiguan; PC4 = Ximen; ST36 = Zusanli; LR3 = Taichong; HRV = heart rate variability; BP = blood pressure, including systolic and diastolic blood pressure; HR = heart rate; MMAS-8 = 8-item Morisky medication adherence scale; SF-12 = 12-item health survey. Figure 2. was created on Biorender with permission to publish.

### 2.6. Primary outcome

The primary outcome will be the change in office SBP among the 3 groups from baseline to the end of the intervention (week 4). The measurement of BP will be performed with an electronic sphygmomanometer (KC2110, Shaanxi Kangshengshi Electronic Technology Co., Ltd., Shaanxi, China). Patients will be required to sit in silence for at least 5 minutes before taking their BP. Keeping the upper arm at the level of the heart, both arms will be measured at baseline and the side with the higher BP will be chosen for subsequent testing. To ensure the accuracy of the recording, the independent outcome assessor will repeat the BP measurement 3 times every 5 minutes and take the mean of the last 2 readings.

### 2.7. Secondary outcomes

Secondary outcomes will involve the change in DBP, mean arterial pressure, heart rate (HR), heart rate variability (HRV), 8-item Morisky medication adherence scale (MMAS-8), and 12-item health survey (SF-12) among the 3 groups at different time points.

The measurement of DBP and HR will be the same as SBP, at baseline, every week, and follow-up. Mean arterial pressure indicates the function of the heart and the resistance of the peripheral aorta, and it can be calculated according to this formula:^[30]^

MAP ​​ ​​ =DBP ​​ ​​ + ​​ ​​ 1/3 ​​ ​​ (SBP ​​ ​​  ​​ ​​ DBP).

Analysis of HRV can reflect the activity, homeostasis, and associated pathology of the cardiac autonomic nervous system.^[31]^ In this trial, HRV will be measured by a flexible dynamic ECG monitor (CH-E31, Zhejiang Zhi Yu Technology Co., Ltd., Zhejiang, China) at baseline, week 1, and week 4. This instrument should be attached to the left chest, about 1 finger from the clavicle, as shown in Figure 2. Before the assessment, the patient will be asked to be relaxed and quiet for at least 10 minutes and will not be verbally informed of the measurement start point, which may affect the results.

The data will be analyzed in the frequency domain from a 5-minute recording, involving low frequency (LF), high frequency (HF), LF/HF ratio, total power, very low frequency, normalized low frequency (LF norm) and normalized high frequency (HF norm).

The MMAS-8, consisting of 8 brief questions, is the most commonly used scale to investigate medication adherence in people with hypertension.^[32]^ The SF-12 is valid and equivalent for Chinese people and consists of physical component summary and mental component summary.^[33]^ Patients are advised to fill out both questionnaires at baseline, week 4, and at follow-up. Supplemental Digital Content 1, http://links.lww.com/MD/J83 shows the above 2 questionnaires.

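### As written, untransformed repeated measures ANOVA would cost power on skewed HRV powers and LF/HF, and three of the seven listed indices probably carry one quantity

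*Protocol article*

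**What the plan says.** Section 2.7 (Secondary outcomes) opens: "Secondary outcomes will involve the change in DBP, mean arterial pressure, heart rate (HR), heart rate variability (HRV"). HRV is measured "at baseline, week 1, and week 4". "The data will be analyzed in the frequency domain from a 5-minute recording", and the indices are LF, HF, "LF/HF ratio, total power, very low frequency, normalized low frequency (LF norm) and normalized high frequency (HF norm"). Neither the normalised units nor a lead index is defined.

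Section 2.10 (Statistical analysis) says that for outcomes measured repeatedly "repeated measures ANOVA and Bonferroni post hoc tests will be used for evaluation". On distribution it says: "Continuous data will be indicated as mean ± standard deviation or median and interquartile range, based on whether the normality is satisfied". The significance rule is "In a 2-sided test at *P* < .05". Section 2.10 mentions no transformation, no rank-based test, no baseline covariate and no adjustment across indices. For categorical data it does offer two tests, chi-square or Fisher's exact.

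**The concern.** HRV is recorded three times, so it falls under the repeated measures ANOVA sentence. The words "based on whether the normality is satisfied" decide how data are summarised, not how they are tested. Read literally, a skewed index would be described by its median and tested on its mean.

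Spectral powers and their ratio are positive and usually right-skewed, and effects on them tend to act multiplicatively. A few large values then dominate the variance on the original scale, and a real shift is harder to detect with 40 patients per group.

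Separately, LF norm, HF norm and LF/HF are probably three expressions of one balance. Reported side by side, one autonomic shift could look like two or three findings, or appear significant on one index and not on another. Section 3.3 hopes that heart rate and HRV will throw some light on how TEAS lowers blood pressure, and the pilot is meant to inform a larger trial. A missed or inconsistent HRV result would be a poor guide.

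**Working it through.** **The plan's own figures.** Section 2.9 gives 3 × 40 = 120, which adds up. It rests on rules of thumb for pilot trials, with no effect size, SD, power or dropout rate. No figure is given for HRV, so there is nothing to reproduce and all variability inputs below are assumptions.

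**Inputs from the article.** Three groups of 40 (2.9); HRV at baseline, week 1 and week 4 (2.7); repeated measures ANOVA, two-sided 0.05 (2.10).

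**Step 1: redundancy (algebra).** Assume u = LF norm = LF/(LF+HF) and v = HF norm = HF/(LF+HF). The same follows if the divisor is total power minus VLF and total power = VLF+LF+HF.
- v = 1 − u. Replacing u by 1 − u reverses the sign of every contrast and leaves every sum of squares unchanged, so F and p are identical.
- LF/HF = u/(1 − u), so ln(LF/HF) = logit(u). LF/HF is a non-linear function of the same quantity, so its ANOVA p-value can differ.

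**Step 2: power under the planned design (simulation).** Group-by-time test with Greenhouse-Geisser correction, 3 × 40 patients, three time points, 2,000 trials per setting. The Monte Carlo standard error is at most √(0.5 × 0.5/2000) = 1.1 points, or about ±2 points. Assumed:
- LF and HF log-normal, with log-SD 0.5, 0.8 or 1.0;
- within-patient correlation 0.5 or 0.7, and LF-HF log correlation 0.5;
- a week-4 shift in ln(HF) of 0.625 log-SD in one TEAS arm, half that in the other and none in usual care, with half of each shift present at week 1.

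The largest shifts are 0.625 × (0.5, 0.8, 1.0) = 0.3125, 0.5 and 0.625, which are HF ratios of e^0.3125 = 1.37, e^0.5 = 1.65 and e^0.625 = 1.87.

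Power in %. The last column is the share of trials in which untransformed LF/HF and LF norm fall on different sides of 0.05.

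| Log-SD | Corr. | HF | ln HF | LF/HF | ln(LF/HF) | LF norm = HF norm | Different sides |
|---|---|---|---|---|---|---|---|
| 0.5 | 0.5 | 54.7 | 59.7 | 40.4 | 57.4 | 58.5 | 24.7 |
| 0.5 | 0.7 | 79.4 | 83.7 | 65.0 | 83.6 | 84.5 | 21.5 |
| 0.8 | 0.5 | 43.2 | 58.4 | 26.6 | 56.4 | 57.2 | 35.9 |
| 0.8 | 0.7 | 64.8 | 81.2 | 42.0 | 81.5 | 81.6 | 42.2 |
| 1.0 | 0.5 | 33.8 | 55.1 | 19.9 | 56.0 | 56.2 | 43.0 |
| 1.0 | 0.7 | 50.1 | 83.1 | 32.2 | 83.7 | 82.8 | 52.4 |

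- Loss for HF: from 83.7 − 79.4 = 4.3 to 83.1 − 50.1 = 33.0 points.
- Loss for LF/HF: from 57.4 − 40.4 = 17.0 to 83.7 − 32.2 = 51.5 points.
- LF norm is within about 1 point of ln(LF/HF) in every row.
- LF norm and HF norm p-values differed by at most about 2 × 10⁻¹⁵, which is rounding.

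The disagreement is mostly the untransformed ratio missing what the normalised pair detects. In the first row, 61.8% of trials had at least one of the three indices significant. LF norm alone was significant in 61.8 − 40.4 = 21.4%, LF/HF alone in 61.8 − 58.5 = 3.3%, and the sum is 24.7%.

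**Step 3: no true effect.** Untransformed HF rejected in 3.1-4.9% of trials and LF/HF in 3.6-5.5%. LF/HF and LF norm disagreed in 4.6-7.4%. At least one of the three was significant in 6.6-8.7%.

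**Step 4: baseline covariate.** For a log-scale outcome with equal variances σ² and baseline correlation ρ, a change score has variance 2(1 − ρ)σ² and a baseline-adjusted value (1 − ρ²)σ². At ρ = 0.5 that is 1.00σ² against 0.75σ²; at ρ = 0.7, 0.60σ² against 0.51σ². Adjustment removes 25% and 15% of the variance respectively.

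LF, VLF and total power were not simulated separately. The argument for HF carries over to them if they are similarly skewed.

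**The case against.** The strongest reply is that the article never says the indices are analysed untransformed. It names a test and is silent on scale. Log transformation followed by repeated measures ANOVA would fit the text, and a full protocol or analysis plan may specify it. Nor does section 2.7 say that each index gets its own hypothesis: HRV is named as one secondary outcome, and the seven indices describe what the recording yields. This stands. It is why the point is conditional on the text being followed as written.

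Four stronger readings are tempting but not supported:
- *The test is invalid or inflates false positives.* It does not; each untransformed test held its level. Seven independent tests would give 1 − 0.95⁷ = 30.2%, but these indices are strongly dependent, and the three balance indices together gave 6.6-8.7%.
- *LF norm and HF norm could contradict each other.* They cannot under the assumed definition. Only LF/HF can part from the pair, and the disagreement meant here is about crossing 0.05, not about direction.
- *All HRV indices lose power.* The normalised units do not, so the list already contains an efficient balance measure.
- *The trial's case on mechanism rests on HRV.* Section 3.3 speaks cautiously, and of heart rate and HRV together.

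The size of the loss is also open. At log-SD 0.5 it is only 4-5 points for HF. If effects on the powers were additive rather than multiplicative, the advantage of logs would shrink.

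What remains is that section 2.10 anticipates non-normal data and responds only in the description, and that no balance index is given priority.

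**Conclusion.** The point holds in a limited, conditional form. Followed as written, the plan's only test for repeated continuous outcomes is valid for HRV but inefficient for right-skewed powers and for LF/HF: about 4-33 points of power for HF and 17-52 for LF/HF. Those figures assume log-normal data, log-SD 0.5-1.0, correlation 0.5-0.7 and a shift of 0.625 log-SD; the article supplies none of these.

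The redundancy of LF norm, HF norm and LF/HF needs no variance assumption, only the usual normalisation, which the article does not define. The practical consequence is one finding that could be counted more than once, or an untransformed ratio that disagrees with the normalised pair on significance (22-52% of simulated trials with an effect).

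This is a worthwhile, cheap improvement to a secondary, mechanistic outcome of a pilot. It does not touch the primary systolic pressure analysis.

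**What to change.** Add to section 2.10:
- LF, HF, VLF, total power and LF/HF are analysed as natural logarithms, with the log baseline value as covariate, and group comparisons are reported as geometric-mean ratios with 95% confidence intervals.
- ln(LF/HF) is the single index of autonomic balance.
- LF norm and HF norm are reported descriptively, without their own tests.

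In section 2.7, define the normalised units. If a full analysis plan already fixes the scale, it is enough to bring section 2.10 into line with it.

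The cost is a few sentences and no new data. Results become ratios rather than absolute units, and two indices lose their own p-value. Little information goes with them, since LF norm and ln(LF/HF) had the same power to within about 1 point.
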